**Method:**

This study is a randomized, single-blind, controlled pilot clinical trial. We divided the patients into two groups: Electroacupuncture (EA) meridian acupoint group and EA non-meridian non-acupoint group. During the study period, both groups will receive routine care and education with an anticipated total of 36 individuals in each group. Both groups of patients will be treated with electroacupuncture (EA) after surgery, and in the morning of the day following the operation, with each session lasting 30 min. Specifically, the EA meridian acupoint group had intervention at the bilateral Zusanli (ST36) and Neiguan (PC6) points, while the EA non-meridian non-acupoints group had selected acupoint interventions at about 1.5 cm from ST36 and PC6. We will use the VAS (Visual Analogue Scale) and abdominal distension grading to evaluate the degree of patients’ postoperative abdominal distension 1–6 h and 24 h after surgery to obtain outcome assessments.

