### Patient recruitment

2.2

This study is expected to include patients who undergo LC at the Department of General Surgery, Putuo Hospital, Shanghai University of Traditional Chinese Medicine, from July 1, 2023 to December 31, 2024. Patients who express interest will be recruited through preoperative interviews and pre-screening. After confirmation by clinical physicians and signing an informed consent form, baseline data will be collected. The criteria for pre-screening were defined as Patients with benign gallbladder diseases requiring LC as outlined in the “Expert Consensus on Surgical Treatment of Benign Gallbladder Diseases in China (2021)” (23) (Figure 1).

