##### Procedure

2.5.2.3

All patients are placed in a supine position and the acupoints are routinely disinfected. The 40 mm disposable sterile acupuncture needle (Hwato, Suzhou, China) was used. The needle was directly punctured 0.5∼1 cun (about 15–30 mm). The acupuncture manipulation is reinforcing and reducing to DeQi. The patient may not be fully awakened at the time of the first acupuncture, so we defined DeQi as the sensation of blockage felt by the acupuncturist during the maneuver. After, use an electric wire to connect both sides of ST36, using a continuous wave type with a frequency of 2 Hz and an intensity of 2–3 mA. There were two times of EA interventions, with the first intervention starting after the surgery, and the second intervention lasting 30 min on the morning of the second postoperative day. When taking the needle, gently press with your hand and use a clean cotton pad to prevent bleeding.

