#### Main outcomes

2.6.1

The primary outcomes are postoperative abdominal distension grading and postoperative abdominal distension VAS score.
1.Postoperative abdominal distension grading: Postoperative abdominal distension is divided into four levels: Grade 0 (score 0): no sense of distension; Grade 1 (score 1): mild distension, slight increase in abdominal wall tension, does not affect rest and sleep; Grade 2 (score 2): moderate distension, high abdominal wall tension, affects rest and sleep; Grade 3 (score 3): severe distension, high abdominal wall tension, unable to rest and sleep. The degree of distension is observed and recorded every hour for 1–6 h and 24 h postoperatively.2.Postoperative abdominal distension VAS score: Postoperative abdominal distension, pain, and nausea will be assessed using the VAS method, with the degree of distension observed and recorded every hour for 1–6 h and 24 h postoperatively.

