#### Secondary outcomes

2.6.2

Secondary outcomes include the time for postoperative abdominal distension to disappear, length of hospital stay, postoperative pain, nausea and vomiting, time to first independent walking, time to first postoperative flatus, time to first postoperative defecation, postoperative complications, and other qualitative indicators for patients.
1.Time for postoperative abdominal distension to disappear: Refers to the difference between the time for postoperative abdominal distension to disappear and the end of the surgery. Patients and their family members should be carefully informed to observe and report the time when the postoperative abdominal distension sensation disappears, and the details should be recorded in the Case Report Form (CRF).2.Postoperative pain, nausea, and vomiting: Postoperative pain and nausea will be assessed using the Visual Analog Scale (VAS). The degree of pain and nausea will be observed and recorded every hour from 1 to 6 h postoperatively and at 24 h, and the frequency of vomiting will be recorded.3.Time to first postoperative flatus: Refers to the difference between the time of the first postoperative flatus and the end of the surgery. Patients and their family members should be carefully informed to observe and report the time of the first postoperative flatus, and the details should be recorded in the CRF.4.Time to first postoperative defecation: Refers to the difference between the time of the first postoperative defecation and the end of the surgery. Patients and their family members should be carefully informed to observe and report the time of the first postoperative defecation, and the details should be recorded in the CRF.5.Length of hospital stay: The time from the end of the surgery to discharge.6.Postoperative complications: Other postoperative complications will be recorded in the CRF.7.Other qualitative indicators for patients.

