### Statistical analysis

2.8

All statistical analyses will be conducted according to the intention-to-treat (ITT) principle, which includes patients who have received at least one session of EA treatment. All paper-based data will be electronically entered and analyzed using SPSS 26.0 (per-protocol set for robustness analysis of the results). In the statistical description, continuous data will be presented as mean ± standard deviation (M ± SD) or median and interquartile range, while categorical data will be presented as frequencies and percentages. Demographic and other baseline data will be compared using ANOVA and chi-square tests. Kaplan–Meier analysis will be used for key times of primary outcomes and secondary endpoints, and group comparisons will be made using the Breslow (generalized Wilcoxon) test. Differences in the incidence rates of nausea, vomiting, and abdominal distension will be compared using chi-square tests or the Mann–Whitney U test. The occurrence rates and severity of compliance will be analyzed using chi-square tests or the Mann–Whitney U test at a significance level of *α* = 0.05. Missing data will be handled using last observation carried forward and multiple imputation.

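### Last observation carried forward is planned beside multiple imputation with no primary method named, and it does not suit distension scores that leave 18 hours between 6 h and 24 h

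*Protocol article*

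**What the plan says.** The Statistical analysis section (2.8) gives one sentence on missing data: "Missing data will be handled using last observation carried forward and multiple imputation". It covers all missing data, does not divide the methods by outcome and calls neither primary nor sensitivity. The same section does give the per-protocol set a supporting role, but neither imputation method gets such a label.

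The outcomes it must serve are in Main outcomes (2.6.1): "The primary outcomes are postoperative abdominal distension grading and postoperative abdominal distension VAS score". For the grade, "The degree of distension is observed and recorded every hour for 1–6 h and 24 h postoperatively", and the VAS follows the same times. Secondary outcomes (2.6.2) include the time until distension disappears, defined as follows: "Refers to the difference between the time for postoperative abdominal distension to disappear and the end of the surgery".

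On scores before 1 h, Patient recruitment (2.2) says: "After confirmation by clinical physicians and signing an informed consent form, baseline data will be collected". The article names no preoperative distension score.

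**The concern.** LOCF assumes that a patient's symptom stays where it was last seen. Here the last gap runs from 6 h to 24 h, and a trial that measures how long distension takes to go does not expect it to stay put. Where the mean changes among patients who lack the 24 h score, the filled arm mean is wrong. If the arms differ in loss or in rate of change, so is the group difference. LOCF also enters the filled value as if it had been measured.

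Multiple imputation uses the patient's other scores and carries the uncertainty of the fill into the standard error. The two methods can therefore give different answers. With no order fixed between them, nothing in the text stops the choice from being made once both are known.

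The stakes are moderate. Section 2.7 calls the trial a pilot whose results will help size a later trial. Section 2.1 also calls it a superiority trial, and section 2.8 sets a 0.05 significance level. A distorted effect would pass into the next sample size.

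**Working it through.** **The plan's own figures.** The missing-data sentence contains no number. The only related figure is the sample size: reading 30 as per arm, 30 × (1 + 0.20) = 36, and 2 × 36 = 72, as stated. The 20% is a recruitment allowance, not a forecast of missing 24 h scores.

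**Gap bridged.** 24 h − 6 h = 18 h for a patient last scored at 6 h, and longer for one last scored earlier.

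**Assumed inputs.** The article gives no means, SDs, missingness rates or VAS range. All values below are assumptions.

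**Step 1: bias in one arm mean at 24 h.** If a share p lacks the 24 h score at random and the mean falls by F from 6 h to 24 h, LOCF overstates the arm mean by p × F.
- F = 1: 0.1 points at p = 10%, 0.2 at p = 20%
- F = 2: 0.2 and 0.4
- F = 3: 0.3 and 0.6

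**Step 2: shift in the difference when both arms fall by the same F.** Shift = (difference in missing share) × F. With 10% versus 30% missing, it is 0.2 × 1 = 0.2, 0.2 × 2 = 0.4 and 0.2 × 3 = 0.6 points. With equal shares it is 0.

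**Step 3: arms that may fall by different amounts.** Let the sham mean go from 5 at 6 h to 3 at 24 h and the EA mean be 2 at 24 h, so the true 24 h difference (EA − sham) is −1.0. The LOCF estimate is −1.0 + p(EA) × F(EA) − p(sham) × F(sham).

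| 6 h difference (EA fall) | 20% / 20% missing (EA / sham) | 10% / 30% | 30% / 10% |
|---|---|---|---|
| 0 (3.0) | −0.80 | −1.30 | −0.30 |
| −0.5 (2.5) | −0.90 | −1.35 | −0.45 |
| −1 (2.0) | −1.00 | −1.40 | −0.60 |

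For example, the first cell is −1.0 + 0.2 × 3 − 0.2 × 2 = −0.8. The errors go both ways, and the parallel, equal-loss cell is exact.

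**Step 4: simulation of LOCF against multiple imputation.** Same means, 36 per arm, SD 1.5, correlation 0.6 between 6 h and 24 h, loss more likely with a higher 6 h score, 20 imputations, 3,000 runs per scenario. Missing shares are nominal.

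| 6 h difference | Missing (EA / sham) | LOCF mean | MI mean | Runs disagreeing at 0.05 |
|---|---|---|---|---|
| 0 | 20% / 20% | −0.79 | −1.01 | 38% |
| −0.5 | 20% / 20% | −0.97 | −1.00 | 23% |
| −1 | 20% / 20% | −1.12 | −1.00 | 15% |
| −0.5 | 10% / 30% | −1.43 | −1.00 | 19% |
| −0.5 | 30% / 10% | −0.50 | −0.99 | 52% |

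In the third row LOCF is off despite parallel change, because loss depends on the 6 h score: the EA arm, with lower 6 h scores, loses fewer patients. Multiple imputation does well here partly because the simulated loss meets its missing-at-random assumption.

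**A limit on the precision argument.** In that third row LOCF rejected in 72.3% of runs and multiple imputation in 72.5%, although LOCF's average effect was larger. Its standard errors were therefore not smaller in this case, since mixing 6 h and 24 h levels adds spread. That LOCF ignores imputation uncertainty is true of the method, but this check does not show intervals that are too narrow.

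**The case against.** The strongest reply is that dividing roles between two named methods is normally left to an analysis plan, which is not shown. That is fair as to roles. A reader might infer that both methods will fill the same values and contradict each other. The text does not say so: they could be split by outcome or used as main and supporting analyses, and they may agree. What stands is that the protocol positively commits to LOCF with no limit on its role.

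Four other stronger readings also fail.

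- **The 1 h score cannot be filled, and is the one most likely to be missing.** The Procedure section does say "The patient may not be fully awakened at the time of the first acupuncture", but in order to define DeQi, not to describe the 1 h assessment. LOCF has no named earlier distension score to carry, yet multiple imputation is in the plan and can fill that value.
- **A 20% loss could decide the primary comparison.** The 20% covers dropout in general. Some of those patients may never enter the analysis set, which requires at least one EA session. Scores end at 24 h, so missingness could be well below 20%. Section 2.8 also names no test of mean VAS at 24 h, and section 2.6.1 no primary time point.
- **LOCF would carry forward a score from before the second session.** This depends on timing that the article gives in two ways: the abstract has "in the morning of the day following the operation, with each session lasting 30 min", the Procedure section "the second intervention lasting 30 min on the morning of the second postoperative day". The two must be reconciled. The 18-hour gap does not depend on them.
- **The primary analysis must become a repeated-measures model.** That goes beyond the defect, and a model for continuous scores does not suit the four-level grade.

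The objection that 10% versus 30% is invented also stands. Patients in both arms are needled and unaware of their group, and nothing in the article points to such an imbalance.

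**Conclusion.** The point holds in limited form and should be corrected. Section 2.8 commits to LOCF for symptom scores that the plan expects to change across a gap of at least 18 hours, and it leaves open which of two methods gives the main result. Bias in an arm mean follows whenever the mean changes among those with missing scores. Bias in the group difference has no fixed direction and is about zero with equal loss and parallel change. The shift of 0.2 to 0.6 VAS points illustrates a fall of 1 to 3 points with 10% versus 30% missing; it is not a forecast. The 15% to 52% disagreement on significance likewise belongs to the simulated scenarios. It does show that the choice between methods can matter at this sample size.

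**What to change.** In section 2.8:

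1. Name multiple imputation as the single primary method for missing distension scores. Include arm and the observed scores at the other time points in the imputation model, and use a method suited to an ordinal outcome for the 0–3 grade.
2. Delete LOCF, or label it a sensitivity analysis only.
3. State that the time outcomes analysed by Kaplan–Meier are censored and not imputed. Kaplan–Meier already implies this, but the missing-data sentence makes no exception for them.

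The cost is a short edit and a little analysis time. No new data or change in sample size is needed. Because multiple imputation carries the uncertainty of the fill, its intervals will usually be slightly wider than those from LOCF, though not in every case, as the third simulated scenario shows.

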## Discussion

3

In recent years, the application of acupuncture in the perioperative period has attracted increasing attention, which is considered part of the enhanced recovery after surgery (ERAS) protocol (17). Acupuncture has great potential in promoting the recovery of human body functions and is currently used in the postoperative stage to promote recovery, alleviate postoperative pain, and prevent common postoperative discomfort such as nausea and vomiting (25). It is worth noting that LC is a relatively simple surgery. Although related discomforts after the surgery, such as abdominal distension and pain, can be managed with relevant medications, the adverse reactions of drugs commonly used for postoperative gastrointestinal dysfunction, such as alvimopan, significantly limit their benefits for patients (26). Therefore, in the context of prioritizing patient-centered care, it is important to select an auxiliary intervention with minimal harm and fewer side effects.

EA is an optional technique. However, it is important to note that the effect of EA on specific acupoints is a significant issue. Therefore, in this study, we selected the acupoints ST36 and PC6 for research. ST36 and PC6 are commonly used acupoints for improving postoperative gastrointestinal function, and studies have shown (27) that palonosetron combined with acupuncture at ST36 and PC6 has a good preventive and therapeutic effect on postoperative nausea and vomiting, and contributes to the recovery of postoperative gastrointestinal function in patients. Therefore, in this study, our aim is to understand whether EA at specific acupoints is truly effective and whether simple acupoint treatment (only two single acupoints) helps improve postoperative abdominal distension and other gastrointestinal dysfunctions and discomfort in patients undergoing LC. Although acupuncture has minimal side effects and is relatively safe, it also presents the issue of pain. The excessive use of acupoints may likely subject patients to more pain during the treatment process, which is also a significant part of the patient's subjective experience. Therefore, the effectiveness of two single acupoints may also provide a reference for simplified acupoint prescriptions. At the same time, we also hope to further confirm the effectiveness of meridian acupoints, thereby providing a foundation for further research.

### Strengths and limitations of this study

3.1

(1) Acupuncture has great potential in promoting the recovery of human body functions and is currently used in the postoperative stage; (2) ST36 and PC6 are commonly used acupoints for improving postoperative gastrointestinal function; (3) The acupuncturists performing the intervention had over ten years of clinical acupuncture experience, which was considered difficult to blind.

## Limitations

4

In this study, there are certain limitations. Firstly, it is a single-center study, which may limit the generalizability of the study results. Secondly, in our study, we were unable to blind the acupuncturist because the acupuncturists performing the intervention had over ten years of clinical acupuncture experience, which was considered difficult to blind (28), so we did not implement blinding of the acupuncturists.

## Data Availability

The original contributions presented in the study are included in the article/Supplementary Material, further inquiries can be directed to the corresponding authors.
